## Methods

### Overview

This will be a single-blind, randomized, 3-arm, parallel-group, clinical trial (2:2:1 allocation ratio). The planned flow diagram for this single-site RCT is presented in Figure 1. The protocol is reported according to the SPIRIT (Standard Protocol Items: Recommendations for Interventional Trials; Checklist 1) [41] checklist. This study was prospectively registered with the Open Science Framework on April 25, 2023.

**Figure 1. F1:**
[figure not shown]
Diagram of planned study flow. DP: direct pointing; MB: mindful breathing; WLC: waitlist control.

### Participants

We will recruit and enroll 173 adults with CMP who meet established eligibility criteria. Sample size estimation was conducted in 2 stages, reflecting an expansion from a sole focus on mechanistic sensitivity to the joint consideration of mechanistic and clinical relevance. The first stage was designed to detect changes in self-transcendence in order to elucidate an emerging therapeutic mechanism of MBIs, whereas the second stage broadened the scope of the study to contribute to a growing body of research evaluating the effects of brief MBIs on chronic pain.

First, our original power analysis using G*Power (Heinrich Heine University Düsseldorf) indicated that a total sample of 138 participants would provide sufficient power (*β*=.80) to detect changes in self-reported and psychophysiological indices of self-transcendence [42]. This target reflected a required analyzable sample of 110, inflated by 25% to account for expected attrition. To promote robust detection of mechanistic effects, we specified a conservative effect size ( Cohen *d*=0.30), representing half the smallest effect observed in our preliminary data (Cohen *d*=0.60). This approach was intended to support the more stringent comparison between the MB and MB+DP groups, while incorporating corrections for multiple comparisons.

Second, to enhance the clinical interpretability of the intervention effects, we added a waitlist control group. This adjustment was made prior to participant enrollment. Inclusion of this no-treatment comparison group provides a benchmark against which to evaluate the specific impact of the MBIs on both mechanistic and clinical outcomes, relative to the natural progression of symptoms in the absence of additional intervention. This control arm was designed to be half the size of each active treatment group (n=35), resulting in a total sample size of 173 and preserving a 2:2:1 randomization ratio. This total sample size (n=173) is consistent with a G*Power estimate for a 3 (group)×2 (time) mixed design, assuming a small effect (Cohen *d*=0.30), 80% power, and a Bonferroni-adjusted alpha of .0125 for 4 pairwise comparisons (ie, self-reported self-transcendence; 2 psychophysiological indices of self-transcendence, including frontal midline theta activity and DMN activity, and acute pain). Beyond these primary group-level effects, the planned sample size also supports Aims 2 and 3. Specifically, a G*Power analysis (2-tailed, *α*=.0167, corrected for multiple comparisons; power=0.80) indicated that 112 participants are sufficient to detect a moderate association (*r*=0.30) among phenomenological and psychophysiological indices of self-transcendence, well below the planned sample of n=173. Finally, this sample size is adequate for the planned mediation analyses; the parallel multiple-mediator model for acute pain includes 19 estimated parameters, yielding approximately 9.1 observations per parameter with n=173, consistent with the commonly cited 5‐10 observations per parameter convention.

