Further, this trial advances the goals of personalized medicine by investigating whether different mindfulness practice instructions produce distinct phenomenological experiences and clinical outcomes. Comparing MB and MB+DP at the level of both phenomenological experience and neural activity advances the goals of mechanism-based treatment personalization. If the two conditions diverge in their effects on self-transcendence but converge on pain outcomes, this would suggest that multiple pathways can produce equivalent clinical benefit and that individual preference and acceptability, rather than specific instructional content, should guide practice selection. Conversely, if MB+DP produces superior outcomes on both mechanistic and clinical indices, this would support a more targeted prescriptive approach, particularly for patients whose pain experience is strongly identity-bound. Either pattern of results would meaningfully inform clinical decision-making in a field that currently lacks guidance on how to match mindfulness instruction style to patient presentation.

The fourth contribution concerns scalability. Demonstrating that just four 30-minute sessions can produce durable reductions in pain interference through three-month follow-up would represent a meaningful addition to the feasibility literature on brief MBIs. In contrast to multiweek programs like MBSR or MORE, which impose substantial time and access burdens, this trial evaluates the effects of just 2 hours of in-person training (across 4 30-minute sessions) paired with 15 minutes of daily practice. An minfulness intervention of this brevity could realistically be integrated into primary care, rehabilitation settings, or digital health platforms. Short, scalable interventions are especially vital for reaching populations with limited access to traditional programs, such as rural residents or those with time, mobility, or financial constraints.

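### The sample of 110 analysable participants does not give 80% power for a 0.30 SD difference between MB+DP and MB; it gives that power for a difference of about 0.60 SD in change

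*Protocol article*

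**What the plan says.** The Participants section of the protocol article gives two stages.

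The first stage, for the two active arms, used G*Power. It states that "a total sample of 138 participants would provide sufficient power", in full "sufficient power (*β*=.80) to detect changes in self-reported and psychophysiological indices of self-transcendence" (the .80 is evidently the power, not beta). The total is built up as a "required analyzable sample of 110, inflated by 25% to account for expected attrition". The effect is a Cohen d of 0.30, called conservative and described as "representing half the smallest effect observed in our preliminary data", which was 0.60. The purpose follows: "This approach was intended to support the more stringent comparison between the MB and MB+DP groups", with corrections for multiple comparisons. The alpha, the test and the pre-post correlation of this stage are not given, nor is it said whether 0.60 and 0.30 are within-person or between-group effects.

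The second stage adds a waitlist arm of 35, for 173 in total at 2:2:1. "This total sample size (n=173) is consistent with a G*Power estimate" for a 3 (group) by 2 (time) mixed design with a small effect (d of 0.30), 80% power and alpha .0125.

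The Statistical Analysis section plans two-sided tests, Bonferroni correction and linear mixed models by group and time, with baseline covariates if needed. On the case where the two mindfulness arms differ on self-transcendence but converge on pain, the Discussion says "this would suggest that multiple pathways can produce equivalent clinical benefit".

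**The concern.** Isolating direct pointing is the stated purpose of the trial, and MB+DP against MB is the only contrast that does it. A reader of the sample-size paragraph will take it that this contrast has 80% power for a small difference. A two-sample comparison at d of 0.30 needs well over 100 per arm, so 55 per arm looked far too few.

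If direct pointing truly adds 0.30 SD, a non-significant result is the more likely outcome under most plausible assumptions. On the pain outcomes, the Discussion sentence would then invite readers to take convergence as evidence of equal benefit, with no equivalence margin stated.

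**Working it through.** **Inputs from the protocol article.** 110 analysable, so 55 per arm; 138 enrolled, so 69 per arm; d of 0.30; preliminary effect 0.60; power 80%; two-sided tests; alpha .0125 for the second stage. **Assumed, because not stated:** pre-post correlation rho; first-stage alpha, tried at .05, .025 and .0125.

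**1. Reproducing 110.** The G*Power formula for a within-between interaction has noncentrality lambda = f² × N × m / (1 − rho). Put f = 0.30/2 = 0.15, m = 2 occasions, two groups, rho = .5:

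- Required N is 90 at alpha .05, 109 at .025 (110 with equal arms, power 80.7%) and 128 at .0125.
- At N = 110, lambda = 0.0225 × 110 × 2 / 0.5 = 9.9.

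So 110 follows from an entered d of 0.30 at alpha .025. It does not follow at .0125, where the same calculation needs 128.

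**2. What that f means.** In a 2 × 2 design, f = (difference in change)/(4 SD). An f of 0.15 is therefore 4 × 0.15 = 0.60 SD. A two-sample t test at d = 0.60 with 55 per arm has squared noncentrality 0.60² × 55/2 = 9.9, the same value, and the same 80.7% power at alpha .025. At rho = .5 the two are one test, because the SD of a change is SD × √(2(1 − rho)) = SD.

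**3. Power at a between-group difference of 0.30 SD.** The noncentrality is 0.30 × √(n/2): 1.573 for n = 55 and 1.762 for n = 69.

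| Per arm | alpha .05 | alpha .025 | alpha .0125 |
|---|---|---|---|
| 55 | 34.5% | 24.6% | 17.2% |
| 69 | 41.7% | 31.0% | 22.5% |

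These apply to an unadjusted comparison, or to change scores at rho = .5. For 80% power the need is 176, 213 or 250 per arm.

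**4. Allowing for the pre-post correlation.** Baseline adjustment turns 0.30 into 0.30/√(1 − rho²), that is 0.346 at rho = .5 and 0.420 at rho = .7.

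| Per arm | rho | alpha .05 | alpha .0125 |
|---|---|---|---|
| 55 | .5 | 43.7% | 24.0% |
| 69 | .5 | 52.4% | 31.3% |
| 55 | .7 | 58.8% | 37.2% |
| 69 | .7 | 68.8% | 47.7% |

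Reaching 80% needs rho of about .79 (69 per arm, adjusted, alpha .05) to .90 (55 per arm, change scores, alpha .0125).

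**5. Detectable difference.** With 55 per arm and 80% power it is 0.54 SD at alpha .05 and 0.65 SD at alpha .0125, unadjusted or in change-score SD units. With baseline adjustment at rho = .5 these become 0.54 × √0.75 = 0.47 and 0.65 × √0.75 = 0.56 SD.

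**6. Second stage.** The 3 × 2 interaction with f = 0.15, rho = .5 and alpha .0125 needs 153; 173 gives 86%. The plan's own retention (110 of 138) applied to 173 leaves 173 × 110/138 = 138. At 138, power is 74.7% if rho = .5 and 80.2% if rho = .55. This is the omnibus test over three groups, not MB+DP against MB.

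**The case against.** The strongest reply is that 110 is a correct answer to a question the paragraph may be asking. The 80% is attached to detecting changes in the indices, and the MB+DP against MB sentence says only what the approach was meant to support. A paired test at d of 0.30 with alpha .025 needs 109, and a three-group interaction with f of 0.15 at alpha .05 needs 111. So a reader who infers that 110 can come only from d of 0.60 goes too far: the figure can be reached from an entered 0.30. That part of the reply stands. It does not rescue the claim. A paired test concerns change within a group, and a three-group omnibus test does not isolate the two active arms. Neither supports the contrast the paragraph names.

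Two other inferences are tempting. One is that the authors undid their own halving of 0.60. That follows only if the preliminary 0.60 was a between-group effect, and the article does not say. The other is that 173 falls short in the second stage. A shift in the assumed rho from .5 to .55 removes the shortfall, and maximum likelihood keeps partial data, so no error is shown there. What remains is that the comparison with 173 ignores the attrition applied in the first stage.

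It is also fair that a condensed article may leave alpha, rho and test family to the full protocol. Their absence is not the complaint. The complaint is that the stated effect, power and sample size do not fit the named comparison at ordinary correlations.

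**Conclusion.** The point holds for a between-group difference of 0.30 SD. MB+DP against MB has about 17-34% power at 55 per arm and 22-42% at 69 per arm (alpha .0125 to .05; unadjusted, or change scores at rho = .5). With baseline adjustment it is 24-52% at rho = .5 and 37-69% at rho = .7. Only an unusually high pre-post correlation, about .79 to .90, would bring 80%. The reconstruction of 110 as f of 0.15 rests on assumed values of rho and alpha; the shortfall does not depend on that reconstruction. The Discussion sentence is conditional and is not an analysis rule, so it is no proof of a planned equivalence claim, but with this power it should be guarded.

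**What to change.** Restate the sample-size paragraph as follows:

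- Say whether 0.60 and 0.30 are within-person or between-group effects, and give the assumed pre-post correlation, the alpha and the attrition.
- State the difference detectable with 80% power for MB+DP against MB at about 55 per arm: about 0.54 SD at alpha .05 or 0.65 SD at alpha .0125, unadjusted or in change-score SD units, and smaller with baseline adjustment.
- Remove the words conservative and small for this contrast.
- Apply the plan's own attrition to 173 before comparing it with the 3 × 2 estimate.
- State that a non-significant MB+DP against MB difference will be reported with its confidence interval and not read as equivalence, and align the Discussion sentence with that.

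The change is text only, with no change in enrolment, and recruitment is still running. The cost is a less favourable stated power and a narrower conclusion from a null result.

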### Hypotheses

The following are our hypotheses:

#### Aim 1

We hypothesize that, from Session 1 to Session 4, both mindfulness groups (MB and MB+DP) will show greater increases in self-transcendence, indexed by higher NADA-S scores and greater frontal midline theta activity (EEG), and greater decreases in DMN activity, indexed by reduced fNIRS-derived fronto-temporal-parietal connectivity, compared to WLC group. We further hypothesize that MB+DP will produce larger increases in these phenomenological and neurophysiological indices of self-transcendence, and larger reductions in DMN activity, relative to MB alone.

#### Aim 2

We hypothesize that phenomenological and psychophysiological indices of self-transcendence will be significantly and coherently related across sessions and groups, such that a higher self-reported self-transcendent state (NADA-S) will be associated with greater frontal midline theta activity (EEG) and lower fNIRS-derived proxy DMN activity within sessions and across Sessions 1-4. We further hypothesize that these associations will be the strongest in the MB+DP group, intermediate in the MB group, and the weakest or absent in the WLC group, reflecting graded coupling between subjective experience and neural indices of self-transcendence as a function of mindfulness instruction type.

#### Aim 3

We hypothesize that treatment-related improvements in pain outcomes will be mediated by increases in self-transcendence and its psychophysiological correlates. Specifically, we expect that assignment to the mindfulness groups, particularly MB+DP, will be associated with lower acute pain intensity at the end of Session 4 and reduced pain-related functional interference through 3-month follow-up via (1) increases in self-reported self-transcendent state (NADA-S), (2) increases in frontal midline theta activity (EEG), and (3) reductions in fNIRS-derived proxy DMN activity measured during Session 4, controlling for presession pain and baseline levels of each mediator [39,40].

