### Statistical Analysis

#### Analysis Plan

The protocol will favor an intention-to-treat approach for the analysis of results. Data analysis will be performed in SPSS (IBM Corp). Baseline demographic information will be summarized using descriptive statistics. Continuous variables will be summarized with means and SDs. Categorical variables will be summarized with counts, proportions, and medians (IQR). The distribution of continuous variables will be assessed using graphical inspection and the Shapiro-Wilk test for normality. If the assumption of normality is not met, equivalent nonparametric approaches or data transformation will be used. The multiple testing problem will be accounted for using Bonferroni correction. All hypothesis tests will be 2-sided, and the familywise Type I error rate will be controlled at α=.05 using Bonferroni-adjusted significance thresholds. If needed, statistical analysis will also be conducted after controlling for baseline demographics and clinical characteristics (eg, age, sex, and race).

The effects of treatment on continuous variables will be evaluated using linear mixed models with fixed effects consisting of a time factor (before to after the experimental session; before treatment to 3-month follow-up) and a between-participants treatment factor (MB vs MB+DP vs WLC, as appropriate). If necessary, we will adjust for randomization imbalance by co-varying baseline variables. Little’s Missing Completely at Random (MCAR) test will be used to determine if data are missing completely at random. We will use maximum likelihood estimation procedures to deal with missing data according to an intent-to-treat philosophy that is robust against common patterns of missing data. The maximum likelihood estimation is based on all data observations; no values are deleted or imputed.

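### The 80% power printed for n=173 belongs to a 3×2 mixed-design test and does not carry over to the two active-versus-waitlist contrasts, which rest on 69 against 35 participants

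*Protocol article*

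**What the plan says.** The Participants section ties the final sample size to one calculation: "This total sample size (n=173) is consistent with a G*Power estimate for a 3 (group)×2 (time) mixed design". The effect entered is a Cohen d of 0.30 and the target power is 80%. The multiplicity adjustment is described as "a Bonferroni-adjusted alpha of .0125 for 4 pairwise comparisons (ie, self-reported self-transcendence", and three more outcomes complete the list. The four items in that list are outcomes (self-report, theta, DMN, acute pain), not contrasts between arms.

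The waitlist size comes from a ratio: "This control arm was designed to be half the size of each active treatment group (n=35), resulting in a total sample size of 173". The Overview confirms a "randomized, 3-arm, parallel-group, clinical trial (2:2:1 allocation ratio". The active arms are therefore 138/2 = 69 each. The same section says the waitlist was added as a benchmark for mechanistic and clinical outcomes.

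Under Hypotheses, Aim 1 expects that "both mindfulness groups (MB and MB+DP) will show greater increases in self-transcendence" than the waitlist, and then that MB+DP exceeds MB. The Analysis Plan adds: "All hypothesis tests will be 2-sided, and the familywise Type I error rate will be controlled at α=.05".

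The first-stage calculation (110 analysable, inflated by 25% to 138) names only the MB versus MB+DP comparison as the one it was meant to support. No power or detectable difference is printed for either active arm against waitlist.

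**The concern.** A three-group, two-occasion mixed design tests group-by-time with a 2-df F statistic. Its usual power calculation takes the total N. It is therefore insensitive to the waitlist holding 35 people, and rejecting it does not show that MB beats waitlist or that MB+DP beats waitlist. The Aim 1 hypotheses are about those contrasts.

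The wording invites the wrong inference. Because the Bonferroni units are called pairwise, a reader may take 80% at d=0.30 to cover the comparisons with waitlist. The stakes are interpretive: someone planning around those contrasts, or reading a non-significant one, would credit the trial with more sensitivity than it has under most plausible inputs.

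**Working it through.** **Inputs from the protocol article.** d=0.30, 80% power, alpha .0125 (0.05/4), two-sided. Arms 69/69/35. Attrition: 110 of 138 retained (110/138 = 0.80), which gives 55/55/28.

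**Assumptions (not stated in the article).** f=d/2=0.15. Pre-post correlation rho=0.5, with 0.4 to 0.7 shown.

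**Step 1: the plan's own figure.** Within-between interaction, noncentral F, lambda = f²·N·2/(1−rho), df 2 and N−3.
- At rho=0.5, lambda = 0.0225·N·4 = 0.09N. This needs N=153 for 80%. At N=173, lambda = 15.57 and power is 86.1%. At 138 analysable it is 74.7%.
- The exact pair (173, 80%) appears at rho of about 0.43.
- The f=d/2, rho=0.5 reading also fits stage 1: two groups at alpha .025 need 109, or 110 when balanced, which is the printed 110. Entering 0.30 directly as f would need only 42 participants, so it does not fit.

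**Step 2: the effect implied for a two-arm contrast.** For two equal groups, equating f²·N·2/(1−rho) with the change-score noncentrality δ²·N/4 gives δ = f·√(8/(1−rho)). In units of the single-occasion SD, multiply by √(2(1−rho)): the result is 4f = 0.60 at any rho. Hence δ = 0.60/√(2(1−rho)) in SDs of change, which equals 0.60 at rho=0.5.

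**Step 3: power of one active arm vs waitlist.** Two-sided noncentral t on change scores, noncentrality δ·√(n₁n₂/(n₁+n₂)), alpha .0125. At rho=0.5 and 69 vs 35: 0.60·√(2415/104) = 2.89 against a critical value of 2.54, so power is 63.7%. At 55 vs 28: 0.60·√(1540/83) = 2.58 against 2.55, so power is 51.5%.

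| rho | 0.60 SD, 69 vs 35 | 0.60 SD, 55 vs 28 | 0.30 SD, 69 vs 35 | 0.30 SD, 55 vs 28 |
|---|---|---|---|---|
| 0.40 | 54% | 43% | 12% | 9% |
| 0.43 | 57% | 45% | 12% | 10% |
| 0.50 | 64% | 51.5% | 14% | 11% |
| 0.60 | 75% | 63% | 18% | 14% |
| 0.64 | 80% | 69% | 21% | 16% |
| 0.70 | 88% | 78% | 25% | 19% |

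**Step 4: f=0.15 read as the three-group effect (rho=0.5).** If both active arms differ from waitlist by D and the waitlist has weight p, then D = 0.30/√(p(1−p)).
- Equal weights (p=1/3): D=0.64 SD, power 70% enrolled and 58% after attrition.
- 2:2:1 weights (p=0.2): D=0.75 SD, power 86% and 75%.
- Graded arms, evenly spaced with MB halfway between waitlist and MB+DP, 2:2:1 weights: MB+DP vs waitlist 0.80 SD (90%, 81%), but MB vs waitlist 0.40 SD (27% enrolled).

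**Step 5: detectable difference.** For 80% power at alpha .0125, solve Step 3 for δ: about 0.70 SD of change at 69 vs 35 and about 0.79 SD at 55 vs 28. At rho=0.5 the SD of change equals the single-occasion SD.

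**Step 6: comparison with the other contrast.** MB+DP vs MB at 0.60 SD and rho=0.5 has 83.8% at 69 vs 69 and 72.7% at 55 vs 55. Before attrition, the shortfall on this reading is confined to the waitlist contrasts.

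**The case against.** The strongest reply is that nothing printed is false. The article says only that n=173 is consistent with a 3×2 estimate. On the reading above that test needs 153, so the statement holds at the enrolled number. The design also matches the planned mixed model with a three-level treatment factor. No sentence assigns 80% to MB vs waitlist or MB+DP vs waitlist, and the text treats MB vs MB+DP as the more stringent comparison. All of this stands. A reader might infer an arithmetic error in 173, or an explicit false claim about the waitlist contrasts. The documents support neither.

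Second, the size of the shortfall rests on inputs the article does not print. This also stands. A reader might take 64% (52% after attrition) as the best case, but it is not a ceiling. At 0.60 SD the enrolled contrast reaches 80% once rho is about 0.64. It also reaches 82% at an unadjusted alpha of .05 (72% after attrition), although that is not the alpha the article states. Reading f=0.15 as the three-group effect gives up to 86% enrolled.

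Third, a reader might infer that a null result against waitlist will be reported as absence of benefit. The article does not say so.

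What the reply does not remove is the mismatch itself: the hypotheses name active-versus-waitlist contrasts, the only power statement for 173 is for another test, and its label is pairwise.

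**Conclusion.** The point holds as a mismatch between the powered test and the hypothesised contrasts. That the powered test is the 2-df interaction is inferred from the named design, since the article does not print the test.

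The 80% cannot be read across to the waitlist contrasts. At the printed d taken literally as a 0.30 SD difference in change, power stays at or below about 25% for every rho up to 0.7. On the more generous f=d/2 reading, the ranges over rho 0.4 to 0.7 are about 54–88% enrolled and 43–78% after attrition. At rho=0.5, none of the effect patterns examined gives both waitlist contrasts 80% after attrition.

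These figures assume a change-score comparison at alpha .0125, equal proportional loss in all arms, and the declared rho and d-to-f conversion. The point does not extend to the MB versus MB+DP contrast.

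**What to change.** In the sample-size text:
- Keep the 3×2 figure, but label it as an omnibus group-by-time figure, and describe the four Bonferroni units as outcomes.
- For each active arm vs waitlist, add power or the detectable difference at the planned allocation. At alpha .0125 and rho=0.5 the detectable difference at 80% power is about 0.70 SD of change at 69 vs 35 and about 0.79 SD at 55 vs 28.
- Declare the assumed pre-post correlation and the conversion from d to f, and show the range over plausible correlations rather than a single power value.
- Do not present the waitlist contrasts as having 80% power at d=0.30.

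The cost is wording only, with no extra participants and no change to allocation. The downside is a less favourable stated power for the waitlist contrasts. Recruitment is expected to run to May 2027, so the text can be amended before results are known.
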